# APOSCREEN-1 – a prospective, single-arm clinical trial for the implementation of a pharmacy-based screening for cardiovascular-kidney-metabolic risk factors in Schleswig-Holstein

**DOI:** 10.1186/s12882-026-05090-x

**Published:** 2026-06-05

**Keywords:** Prevention, Cardiovascular risk, Chronic kidney disease, Diabetes, Hypertension, Point-of-care testing, Community pharmacy, Public health

## Abstract

**Background:**

Cardiovascular-kidney-metabolic (CKM) syndrome has emerged as a major global health burden and driver of cardiovascular disease (CVD), the leading cause of death worldwide. Effective management of CKM depends on timely identification of underlying risk factors. Nevertheless, participation rates in primary care-based screenings are low. Consequently, CKM syndrome oftentimes remains undetected until organ damage is clinically present. Community pharmacies offer an accessible, yet underused, setting to enhance early detection. APOSCREEN-1 evaluates the feasibility and diagnostic yield of a pharmacy-based multi-parametric screening for cardiovascular-kidney-metabolic health.

**Methods:**

APOSCREEN-1 is a prospective single-arm clinical trial conducted in 20 community pharmacies in the German state of Schleswig-Holstein. Adults (*n* = 1000) aged ≥ 40 years with predefined risk criteria are included. Participants undergo standardized point-of-care testing (glycated hemoglobin, lipid profile, urinary albumin, blood pressure). Additionally, clinical history is assessed and results are transmitted to the study center via an online platform. Patients meeting pre-defined thresholds of the tested parameters are followed up by confirmatory laboratory testing at the study center or at the participants’ general practitioner. Primary outcomes include completion rate, implementation metrics from the pharmacy perspective, and the number needed to screen to detect unknown or insufficiently managed cardiometabolic risk factors. Secondary outcomes comprise participant metrics, diagnostic metrics of the screening, evaluation of the clinical impact.

**Discussion:**

This study aims to address the unmet need for scalable prevention of CVD by identification of CKM syndrome risk factors outside traditional primary care settings. Evidence on feasibility, acceptance, and diagnostic benefit may support the use of community pharmacies as an additional access point for early CKM syndrome detection. Future interventional studies will be required to evaluate structured follow-up pathways and long-term effectiveness.

**Trial registration:**

This study was registered with the German trial registry (Deutsches Register klinischer Studien) on 29.01.2026, under trial number DRKS00039149.

**Supplementary Information:**

The online version contains supplementary material available at 10.1186/s12882-026-05090-x.

## Background

Cardiovascular disease (CVD) remains the leading cause of death worldwide [1]. Its development is driven predominantly by cardiovascular risk factors, including obesity, smoking, arterial hypertension, diabetes mellitus, and hypercholesterolemia. Chronic kidney disease (CKD) further amplifies cardiovascular risk and represents an independent risk factor. The interplay and combination of these factors have been defined as cardiovascular-kidney-metabolic (CKM) syndrome [2, 3].

The prevalence of the CKM syndrome is rising substantially [4]. In industrialized countries, 6–13% of the population are affected by advanced CKM syndrome stages involving organ damage, which corresponds to an estimated 5–11 million individuals in Germany. In the long-term, CKM syndrome shortens life expectancy, reduces social or occupational participation and is a major public health burden [5, 6].

Germany exemplifies this trend: despite the highest healthcare expenditure in the EU (11,7% of GDP in 2023), life expectancy remains below average due to CVD [7, 8]. Currently ranked only 17th out of 27 EU countries, Germany’s average life expectancy of 81.1 years has fallen below the EU average since 2010. This discrepancy suggests that Germany’s healthcare system fails to convert spending into better health outcomes.

Early identification of CKM syndrome is essential to avoid organ damage [9, 10]. In Germany, a nationwide preventive health check-up program exists to facilitate early detection of CKM syndrome and its contributing conditions. However, despite the long-standing availability of such programs, participation rates remain low with only 50% of the German population participating regularly [11]. Therefore, a large proportion of individuals remain undiagnosed until clinical manifestation occurs: approximately 49–84% of CKD cases, 20% of arterial hypertension, 22% of diabetes mellitus, and more than 50% of dyslipidemia cases remain undetected in the general population [12–14]. This underscores the urgent need for more effective and accessible screening strategies.

The approximately 16.800 German community pharmacies represent a trusted healthcare resource for the public, and are frequently visited with 64% of the population visiting at least once per month [15]. Pharmacists are highly trained healthcare professionals that may support the healthcare system with clinical services but remain an underutilized resource in this regard.

The APOSCREEN-1 concept, developed in collaboration with the Pharmacists’ Association of Schleswig-Holstein, aims to address this critical gap in secondary prevention by implementing a low-threshold, risk-based, and multi-parametric screening approach in community pharmacies.

## Methods/design

### Study aim and design

The APOSCREEN-1 study is a single-arm clinical trial conducted in community pharmacies located in the federal state of Schleswig-Holstein, Germany. The study aims to assess the feasibility and diagnostic yield of a multi-parametric, pharmacy-based, risk-adapted point-of-care (PoC) screening for CKM syndrome risk factors. It follows a two-step approach: first, a pragmatic point-of-care screening in pharmacies is conducted to triage patients with high cardiovascular risk who may benefit strongly from further diagnostic work-up. In a second step, these patients undergo detailed confirmatory testing and receive guideline-based therapeutic recommendations. Ethical approval has been obtained from the local institutional review board (AZ D616/25).

### Study setting and pharmacy selection

The study takes place in the outpatient setting with a planned number of 20 participating pharmacies. This number was chosen pragmatically for the pilot implementation phase to balance sufficient recruitment capacity with feasibility of onboarding, monitoring, technical support, and confirmatory follow-up. Each pharmacy is expected to recruit approximately 50 participants, resulting in a total planned sample size of 1,000 participants.

Pharmacies will be selected in collaboration with the Pharmacists’ Association of Schleswig-Holstein. The Association invited community pharmacies in Schleswig-Holstein to express interest in participation. From this pool of interested pharmacies, sites will be selected purposively according to predefined implementation-relevant criteria. First, we aim to include 10 pharmacies located in the region of the study center and 10 pharmacies located at greater distance from the study center. Second, within each of these two groups, we aim to include five pharmacies with customer restroom facilities allowing on-site urine albumin-creatinine ratio (UACR) testing and five pharmacies without such facilities, resulting in 10 pharmacies with and 10 pharmacies without on-site UACR testing capacity. Third, pharmacies will be selected to ensure broad geographic coverage across Schleswig-Holstein, including northern, southern, western, and eastern regions of the federal state.

This selection strategy is not based on random sampling and is not intended to generate a representative sample of all German community pharmacies. Rather, it is a purposive implementation-oriented sampling strategy designed to capture relevant heterogeneity in pharmacy infrastructure, distance to the study center, and regional accessibility within Schleswig-Holstein.

### Primary outcomes

The study will assess three primary outcomes:

(I)Participant-level feasibility is assessed by screening completion rates of participants who provided informed consent. The outcome is defined as completion of the structured questionnaire, performance of blood pressure measurement and PoC-testing for dyslipidemia and HbA1c. The study aims for an overall completion rate ≥ 70% based on the reported use of primary care screenings and prospective feasibility on the national level in Germany.(II)Implementation outcomes from the pharmacy perspective are evaluated for the implementation domains acceptability, feasibility, and sustainability. The outcome is evaluated using validated instruments, including the Acceptability of Intervention Measure (AIM), the Feasibility of Intervention Measure (FIM), and the Normalization Measure Development Questionnaire (NoMad) to assess sustainability (Supplementary Tables 1 and NoMad Questionnaire) [16–19]. These instruments use standardized self-administered questionnaires completed by pharmacy staff that are rated on Likert scales. Validated German versions will be used. For each domain, the outcome criterion is defined by a null hypothesis assuming a median Likert-scale score ≤ 3. Rejection of the null hypothesis will be interpreted as evidence of sufficient implementation performance under routine practice conditions.(III)The medical screening yield is quantified by the number needed to screen (NNS) to identify at least one previously unknown or insufficiently managed CKM syndrome risk factor. These are defined as non-HDL cholesterol ≥ 5.7 mmol/L for known dyslipidemia or lipid-lowering therapy, HbA1c ≥ 8.5% in participants with known diabetes mellitus, positive albuminuria test without RASi or SGLT2i therapy in participants with CKD, or blood pressure ≥ 140/80 mmHg for participants with known hypertension. A NNS ≤ 5 will be considered as indicative of a clinically meaningful detection efficiency of the multi-parametric screening approach. Further, a NNS between 5 and 10 will be considered an exploratory finding indicating the need for potential refinement or modification of the screening strategy. An observed NNS > 10 will be interpreted as an unfavorable feasibility outcome under routine practice conditions.

An NNS of ≤ 5 was predefined as a pragmatic threshold for clinically meaningful detection efficiency. This threshold reflects the identification of one previously unknown or insufficiently managed actionable risk factor in 20% of screened at-risk individuals. Although this is not directly comparable to outcome-based NNS estimates from established screening programs, it is expected to correspond to a downstream NNS to prevent one clinical event of approximately 100–150, assuming that detected abnormalities trigger evidence-based treatment with numbers needed to treat of around 20–30. Against this background, and considering that accepted screening programs often operate with substantially higher outcome-based NNS values, an NNS ≤ 5 was considered a clinically relevant benchmark for this pilot study [20].

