### Confirmatory testing

Participants are invited to undergo confirmatory assessment if screening results meet at least one of the predefined thresholds: systolic blood pressure ≥ 140 mmHg and/or diastolic blood pressure ≥ 90 mmHg, positive urine albuminuria test (corresponding to an albuminuria ≥A2 and urine-albumin-creatinine-ratio of ≥ 30 mg/g), a non-HDL-C ≥ 5.7 mmol/l or HbA1c ≥ 5.7% for patients without and ≥ 8.5% for patients with known diabetes (Supplementary Figures S1-4 [23–26]). In case of critical values at screening, pharmacists will be guided by an emergency algorithm (Supplementary Figure S5).

Confirmatory testing will be performed at the study center to enable standardized reassessment. To ensure representative coverage of both urban and rural regions, participating pharmacies will be selected accordingly, allowing the study to capture regional heterogeneity in patient presentation and healthcare access. In this context, ten pharmacies located at greater geographical distance (> 30 km) from the study center will be included.

At the study center visit, all previously screened parameters will be reassessed using standardized laboratory methods. In addition, 24-hour ambulatory blood pressure monitoring (ABPM) or 7-day home-based blood pressure monitoring (HBPM) will be conducted. Blood measurement of creatinine, CRP and lipoprotein(a) will be taken for improved precision of the risk assessment. The patient pathway is visualized in Fig. 1.

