Implementation outcomes will be analyzed separately for each implementation instrument and domain. AIM, FIM, and NoMad assess conceptually distinct implementation constructs, including acceptability, feasibility, and normalization/sustainability. Therefore, no combined implementation score or omnibus test will be used. For each domain, median Likert-scale scores and interquartile ranges will be reported. In addition, one-sided one-sample Wilcoxon signed-rank tests will be used to assess whether domain scores exceed the neutral midpoint of the scale, using the null hypothesis that the median domain score is ≤ 3. Given the exploratory nature of this pilot implementation study and the domain-specific interpretation of implementation outcomes, no formal multiplicity adjustment is planned. Results will be interpreted separately by domain and in the context of the overall implementation pattern.

The unadjusted NNS will be calculated as the number of participants with completed screening divided by the number of participants with at least one previously unknown or insufficiently managed CKM risk factor identified during screening. For primary outcome, a pre-specified PPV-adjusted NNS will be calculated using the positive predictive value estimated among screen-positive participants undergoing confirmatory testing at the study center. Participants without available confirmatory testing will not be included in the estimation of the PPV. Stratified NNS according to pharmacy-prompted or self-referral recruitment will be further reported.

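### The NNS definition lists criteria only for people with a known or treated condition, so read literally no previously unknown risk factor can count

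*Protocol article*

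**What the plan says.** Primary outcomes (III) sets the target of the NNS and opens its definition in these words: "to identify at least one previously unknown or insufficiently managed CKM syndrome risk factor. These are defined as non-HDL cholesterol". The four criteria are:

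- Lipids: "These are defined as non-HDL cholesterol ≥ 5.7 mmol/L for known dyslipidemia or lipid-lowering therapy".
- Glucose: "HbA1c ≥ 8.5% in participants with known diabetes mellitus".
- Kidney: "positive albuminuria test without RASi or SGLT2i therapy in participants with CKD".
- Blood pressure: ≥ 140/80 mmHg, "for participants with known hypertension".

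An NNS of at most 5 is favorable, 5 to 10 is exploratory, and above 10 is unfavorable.

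Sample size and statistical analysis computes the unadjusted NNS as completed screenings "divided by the number of participants with at least one previously unknown or insufficiently managed CKM risk factor identified during screening". It gives no thresholds there. It makes a PPV-adjusted NNS the primary version, with the PPV taken from screen-positive participants who are confirmed at the study center.

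Confirmatory testing has its own list, introduced by "Participants are invited to undergo confirmatory assessment if screening results meet at least one of the predefined thresholds". That list does reach people without a diagnosis. HbA1c counts from 5.7% without known diabetes and from 8.5% with it, non-HDL-C counts from 5.7 mmol/l in everyone, and blood pressure counts from 140 systolic and/or 90 diastolic.

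**The concern.** The definition does not match its label. The label covers two groups, people with an undetected factor and people whose known factor is poorly controlled. The criteria cover only the second group. Someone with no diabetes diagnosis has no HbA1c value that would count, and the same holds for lipids and blood pressure in people without the diagnosis or treatment.

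This is the numerator of a primary outcome with fixed decision bands, and finding undetected disease is the main reason for the screening. If the referral thresholds are meant to fill the gap, the endpoint includes every HbA1c from 5.7% in people without known diabetes. That is a much wider net than the 8.5% printed in the definition, and nothing in the article says that it applies to the NNS.

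**Working it through.** **1. Reproduce the plan's own figures.** NNS 5 means a yield of 1/5 = 20%, as stated. The downstream figure is 5 × 20 = 100 to 5 × 30 = 150, as stated. Expected referrals in the study-center region are 10 pharmacies × 50 participants × 0.50 = 250. With 20% attrition this is 250 × 0.80 = 200. Both match. The arithmetic is sound; the problem is what is counted.

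**2. Check each criterion for a route by which an unknown factor could enter.**

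| Parameter | NNS definition applies to | Referral rule applies to |
|---|---|---|
| Non-HDL-C | known dyslipidemia or lipid-lowering therapy | everyone |
| HbA1c | known diabetes | with and without known diabetes, at different cut-offs |
| Albuminuria | CKD, without RASi or SGLT2i | any positive test |
| Blood pressure | known hypertension (140/80) | everyone (140 and/or 90) |

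The albuminuria criterion says CKD without the word known. But Table 2 collects creatinine and cystatin C only at confirmatory testing, so at screening CKD status rests on reported history. A positive test in someone with no CKD on record is not covered.

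**3. Compare with the other sections.** The paragraph that justifies the threshold of 5 and the NNS formula both repeat the two-part target. Missing data needs each factor classified as known, unknown, controlled or insufficiently managed. The Discussion describes the NNS as being for a factor not observed before. All four need unknown factors to count.

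**4. Size.** Let T be the share of completers who are referral-positive. The plan's 50% is used for T, as a proxy. Let s be the share of those positives who also meet a listed known-condition criterion. The documents give no value for s, so a range is shown.

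- All referral-positives count: NNS = 1/T = 1/0.50 = 2.
- Literal list: NNS = 1/(T × s) = 2/s.

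| s (assumed) | Unadjusted NNS, literal list | Band |
|---|---|---|
| 0.5 | 4.0 | ≤ 5 |
| 0.4 | 5.0 | ≤ 5 |
| 0.3 | 6.7 | 5–10 |
| 0.2 | 10.0 | 5–10 |

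The favorable band is lost when 2/s > 5, that is s < 0.4. The unfavorable band is reached only when 2/s > 10, that is s < 0.2. The formula takes everyone on the list to be referral-positive as well. For blood pressure this depends on how 140/80 is read: anyone with known hypertension who qualified on a diastolic value of 80 to 89 alone would add to the literal numerator without being referred.

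**5. The primary version.** The article gives no formula for the PPV adjustment. Taking it as the unadjusted NNS divided by the PPV, the results are 2/PPV when all referral-positives count and 2/(s × PPV) under the literal list. Both are higher than the unadjusted values for any PPV below 1. The first stays at or below 5 if PPV ≥ 0.4, and the second if s × PPV ≥ 0.4.

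**6. Match between the PPV and the numerator.** The PPV comes from people sent for confirmation under the referral rule. A participant with CKD on a RASi and a positive albuminuria test is in that set but not on the NNS list. So is a participant without known diabetes whose HbA1c is 5.7%. If the list is the numerator, the PPV describes a different group from the one it adjusts.

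**The case against.** The strongest reply is that the intent is evident. Counting only known conditions would empty half of the endpoint's own name and contradict four other places. The shared values of 8.5% and 5.7 mmol/L suggest that the list is the known-condition part of the same scheme as the referral rule. The PPV adjustment also ties screen-positive status, and so the referral rule, indirectly to the NNS. Much of this stands: unknown factors are plainly meant to count. What it leaves open is which thresholds decide that an unknown factor is present. The indirect tie through the PPV does not say so, and the two lists differ in ways that shared values do not resolve.

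Three stronger inferences are tempting, and the documents do not support them:

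- That the investigators plan to ignore undiagnosed disease. The other sections exclude this.
- That the choice of reading moves the result across all three bands. The illustrative values 2, 4 and 10 reach only two, since 10 is not above 10. Movement beyond that needs s < 0.2, for which the documents offer no evidence. Prescribed medication is an inclusion criterion and a prompted recruitment route, so known conditions should be common in this sample.
- That the rule will be chosen after the data are seen. The full protocol, any SAP and the supplementary figures are not shown and may settle it.

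The possibility of an SAP does not remove the point, however. The article does not leave the definition open. It states one that is wrong for half of its target, and an SAP that counted unknown factors would contradict it.

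**Conclusion.** The point holds as an internal contradiction in a primary-outcome definition. The stated criteria give previously unknown factors no way into the NNS numerator, contrary to the outcome's label and to the threshold rationale, the NNS formula, the Missing data section and the Discussion. The real ambiguity is which thresholds apply to people without a diagnosis.

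On the plan's 50% expectation, the unadjusted NNS is 2 if every referral-positive counts and 2/s under the literal list. The ≤ 5 conclusion changes only if fewer than 40% of positives meet a listed criterion. That share is an assumption, so the calculation shows that the reading can decide the band, not that it will. The primary PPV-adjusted value is higher under both readings.

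**What to change.** Before analysis, rewrite the definition in two explicit parts: (a) insufficiently managed, and (b) previously unknown, with an endpoint threshold for each parameter in participants who have neither the diagnosis nor matching medication. In the same text:

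- State whether the referral thresholds count for the NNS, including HbA1c from 5.7% without known diabetes.
- Make the screen-positive set used for the PPV the same as the set in the NNS numerator.
- Reconcile the blood pressure thresholds in Primary outcomes (140/80) and Confirmatory testing (140 and/or 90). Placing the two lists side by side unchanged would build that conflict into the endpoint. Which values apply is for the investigators to decide.

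The cost is protocol or SAP wording only. Diagnoses, medication and all screening results are already collected in the eCRF (Table 2).

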### Sample size and statistical analysis

The planned sample size of 1000 participants allows for reliable estimation of key outcomes with 95% confidence intervals with an estimation error of approximately ± 5%. With an expected prevalence of 50% of risk factors and 10 pharmacies in the region of the study center, we expect 250 participants with indication for confirmatory testing at the study center. At an expected attrition of 20%, 200 participants should complete confirmatory testing. This allows for determination of false-positive rates and test specificity with acceptable precision (± 10%). Attrition in the GP-confirmatory testing arm is expected to be higher, but will be minimized through repeated digital or telephone prompts and, if necessary, invitation for testing at the study center. Statistical analysis will be descriptive, using frequency tables, means (± standard deviation), medians (± interquartile range) for Likert-Scale analysis, and proportions with 95% confidence intervals. Diagnostic metrics (sensitivity, specificity, PPV, NPV) will be determined. Sensitivity of the PoC test can be assessed based on the results from the confirmatory testing. Scale scores for implementation metrics will be calculated as the mean of the respective items, with higher values indicating greater agreement and lower values indicating greater disagreement.

Feasibility and clinical outcomes will be summarized overall and, where appropriate, descriptively at pharmacy level. Pharmacy-level summaries will include recruitment numbers, screening completion rates, confirmatory testing uptake, diagnostic yield, and implementation scores. Baseline pharmacy characteristics will be used to contextualize variation across pharmacies, whereas pharmacy-level implementation process metrics will be interpreted as outcomes of the implementation process. Given the limited number of participating pharmacies, these analyses will be exploratory and hypothesis-generating. Confirmatory inference regarding pharmacy-level predictors is not planned.

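### The primary NNS definition uses 140/80 mmHg for known hypertension, but the confirmatory-testing rule uses 140 and/or 90 mmHg, and the difference is not explained

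*Protocol article*

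**What the plan says.** Primary outcomes (III) in the protocol article defines the screening yield as the NNS to find at least one unknown or insufficiently managed risk factor. For blood pressure, the limit for insufficient management is "140/80 mmHg for participants with known hypertension". The section does not say whether one component is enough or both are needed. An NNS of 5 or less is the success criterion, which the article equates with a yield of 20%.

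The Confirmatory testing section invites participants whose screening shows "systolic blood pressure ≥ 140 mmHg and/or diastolic blood pressure ≥ 90 mmHg". This applies whether or not hypertension is already known. In the same sentence, where a cut-off does depend on known disease, the text says so: "HbA1c ≥ 5.7% for patients without and ≥ 8.5% for patients with known diabetes".

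Sample size and statistical analysis then adjusts the primary NNS "using the positive predictive value estimated among screen-positive participants undergoing confirmatory testing at the study center".

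**The concern.** The two sections give different diastolic limits for what should be one screen-positive state, and the article text does not say why. One of the two limits sits inside a primary outcome with a preset success criterion.

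The neighbouring cut-offs suggest a slip. Non-HDL cholesterol is 5.7 mmol/L in both sections, and HbA1c in known diabetes is 8.5% in both. Blood pressure is the only numeric cut-off that differs.

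The conflict matters even if 80 is deliberate. On the either-component reading, some participants count as detected cases in the NNS but are never sent for confirmation on account of that finding. The yield is then higher than the study's own screen-positive rule would give. The PPV adjustment is also applied to cases on which no PPV could be estimated. Until one limit is fixed, the choice between 80 and 90 could be made after the results are known.

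**Working it through.** **Step 1: the two rules side by side**

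| Parameter | NNS definition, known disease (Primary outcomes III) | Trigger (Confirmatory testing) | Same number? |
|---|---|---|---|
| Non-HDL cholesterol | 5.7 mmol/L | 5.7 mmol/L | yes |
| HbA1c, known diabetes | 8.5% | 8.5% | yes |
| Albuminuria | positive test in CKD without RASi or SGLT2i | any positive test | no numeric difference |
| Blood pressure | 140/80, and/or not stated | 140 and/or 90 | **no** |

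**Step 2: the plan's own figures.** An NNS of 5 is a yield of 1/5 = 20%. For confirmatory testing, 500 × 0.50 = 250 and 250 × 0.80 = 200. These agree with the article and do not depend on the diastolic limit, so no sample-size figure is affected.

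**Step 3: how many more known hypertensives are flagged at 80.** The documents give no blood-pressure distribution. Assumptions for known hypertension: bivariate normal, systolic SD 16, diastolic SD 10, correlation 0.6, either component sufficient.

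| Assumed mean | P(SBP ≥ 140 or DBP ≥ 90) | P(SBP ≥ 140 or DBP ≥ 80) | Difference |
|---|---|---|---|
| 130/76 | 0.289 | 0.437 | 0.148 |
| 132/78 | 0.340 | 0.510 | 0.170 |
| 135/80 | 0.415 | 0.592 | 0.177 |
| 138/82 | 0.494 | 0.671 | 0.177 |

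With the correlation between 0.4 and 0.8, the difference ranges from 0.126 to 0.190.

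**Step 4: effect on the overall yield.** Assume 40–60% of participants have known hypertension.

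- Upper bound, if nobody in the added group has another finding: 0.148 × 0.4 = 0.059 to 0.177 × 0.6 = 0.106.
- If 40% already count through another finding, taken as independent: multiply by 0.6, giving 0.036 to 0.064.

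**Step 5: effect at the planning figure.** The article plans "With an expected prevalence of 50% of risk factors and 10 pharmacies in the region of the study center". Take that 50% as the NNS yield at 140/90 (an assumption), and take adjusted NNS = NNS/PPV (also an assumption). The adjusted NNS equals 5 when PPV = 0.20/yield.

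| Yield | NNS = 1/yield | PPV at which adjusted NNS = 5 |
|---|---|---|
| 0.500 (140/90) | 2.00 | 0.40 |
| 0.536 | 1.87 | 0.373 |
| 0.564 | 1.77 | 0.355 |
| 0.606 (upper bound) | 1.65 | 0.33 |

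The unadjusted verdict is the same at either limit. The adjusted verdict depends on the limit only if the PPV falls between about 0.36 and 0.40, or between 0.33 and 0.40 at the upper bound.

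**Step 6: effect when the yield is far below plan.** With 40% known hypertension, mean 130/76, and 5% of participants with another finding:

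- at 140/90: 1 − (1 − 0.4 × 0.289) × 0.95 = 0.160, NNS 6.3
- at 140/80: 1 − (1 − 0.4 × 0.437) × 0.95 = 0.216, NNS 4.6

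These lie on opposite sides of the limit of 5.

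**Step 7: a check without a distributional model.** Let h be the share with known hypertension and q the share of those with systolic below 140 and diastolic 80–89, independent of other findings. Then yield at 80 = yield at 90 + h × q × (1 − yield at 90). For a yield of 18% at 140/90 (NNS 5.56, criterion missed):

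- h = 0.4, q = 0.05: 0.18 + 0.4 × 0.05 × 0.82 = 0.196, NNS 5.1
- h = 0.6, q = 0.30: 0.18 + 0.6 × 0.30 × 0.82 = 0.328, NNS 3.1

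**The case against.** The two lists serve different purposes: one defines poor management, the other decides who is worth a work-up. They already differ for albuminuria, where the NNS definition carries a treatment condition that the trigger lacks. The Discussion also says the triage should avoid too low a threshold for further work-up. A management limit below the work-up trigger is therefore conceivable, and Fig. 1 or Supplementary Figures S1–4, which were not available here, might explain it. This stands as a reason not to assert a typing error. It does not remove the problem, because a deliberate 80 still creates NNS cases that meet no trigger and cannot inform the PPV.

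The direction of the bias depends on a reading the article does not state. If both components must be exceeded, every blood-pressure case has systolic of at least 140 and is sent for confirmation. With the same assumed inputs (130/76, correlation 0.6), 17.4% would then be flagged against 28.9% under 140 and/or 90, so the yield would be understated instead. This stands too. The two sections still disagree, only in the other direction.

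If 90 is what will actually be applied, there is no bias, only a misprint.

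The low-yield example is also sensitive. If 10% rather than 5% have another finding, the NNS is 4.9 at 140/90 and 3.9 at 140/80, and both pass. In a population selected for smoking, obesity or risk medication, more than 5% is plausible.

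Finally, this is a pilot with a largely descriptive analysis and an NNS limit it calls pragmatic. The eCRF holds the blood-pressure readings, so the NNS can be recomputed at either limit. Recomputing afterwards does not settle which result is primary, however, and so the limit needs fixing beforehand.

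**Conclusion.** The concern holds. A threshold in a primary outcome conflicts with the study's own rule for a positive screen, the article text does not explain the difference, and the and/or logic is missing. Confidence in the mismatch is high. Whether 80 is a misprint or intended cannot be settled from the article.

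The size of the effect rests on assumed blood-pressure means, SDs and correlation, an assumed 40–60% with known hypertension, independence of findings, and the either-component reading. On those terms the overall yield rises by about 4–6 percentage points when 40% of participants have another finding, and by at most 6–11 points otherwise. At the planned 50% this does not change the conclusion on its own. It becomes decisive only for a yield near 20% or a PPV in the narrow range shown above. The point should be corrected, but it does not threaten the trial.

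**What to change.** Before outcome data are seen, correct Primary outcomes (III) so that a single blood-pressure criterion for known hypertension governs both the NNS case definition and the invitation to confirmatory testing. State explicitly that either component suffices. The simplest version is systolic ≥ 140 and/or diastolic ≥ 90 mmHg in both places. Check Fig. 1 and the supplementary figures against it.

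If the investigators deliberately keep 80 for the NNS, they should justify it and also report the NNS at 140/90.

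The cost is a one-line correction. On the either-component reading, 140/90 makes the NNS slightly less favourable. Using 140/80 for both purposes would instead raise the confirmatory workload. No stated sample-size figure changes when 80 is corrected to 90.
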